## Abstract

**Introduction:**

Following cardiac surgery, patients currently attend an outpatient review 6 weeks after hospital discharge, where recovery is assessed and suitability to commence cardiac rehabilitation (CR) is determined. CR is then started from 8 weeks. Following a median sternotomy, cardiac surgery patients are required to refrain from upper body exercises, lifting of heavy objects and other strenuous activities for 12 weeks. A delay in starting CR can prolong the recovery process, increase dependence on family/carers and can cause frustration. However, current guidelines for activity and exercise after median sternotomy have been described as restrictive, anecdotal and increasingly at odds with modern clinical guidance for CR. This study aims to examine the feasibility of bringing forward outpatient review and starting CR earlier.

**Methods and analyses:**

This is a multicentre, randomised controlled, open feasibility trial comparing postoperative outpatient review 6 weeks after hospital discharge, followed by CR commencement from 8 weeks (control arm) versus, postoperative outpatient review 3 weeks after hospital discharge, followed by commencement of CR from 4 weeks (intervention arm). The study aims to recruit 100 eligible patients, aged 18–80 years who have undergone elective or urgent cardiac surgery involving a full median sternotomy, over a 7-month period across two centres. Feasibility will be measured by consent, recruitment, retention rates and attendance at appointments and CR sessions. Qualitative interviews with trial participants and staff will explore issues around study processes and acceptability of the intervention and the findings integrated with the feasibility trial outcomes to inform the design of a future full-scale randomised controlled trial.

**Ethics and dissemination:**

Ethics approval was granted by East Midlands—Derby Research Ethics Committee on 10 January 2019. The findings will be presented at relevant conferences disseminated via peer-reviewed research publications, and to relevant stakeholders.

**Trial registration number:**

ISRCTN80441309

Strengths and limitations of this studyThis is one of the first studies to look at the timing of follow-up and cardiac rehabilitation after cardiac surgery.This feasibility study is a small multicentre randomised controlled trial (RCT).The study will collect both qualitative and quantitative data.If it is determined that a larger scale RCT is feasible, this study will generate valuable data to enable its design.This feasibility study is not large enough to determine effectiveness or cost-effectiveness and is limited to assessing the feasibility of a larger trial.

## Introduction

Following cardiac surgery, patients currently attend their first outpatient review 6 weeks after hospital discharge, where recovery is assessed and ability to commence cardiac rehabilitation (CR) is determined. CR is then started from 8 weeks. In a 2017 survey, 35 of the 42 UK cardiac centres who responded, confirmed this as current practice.^1^ This interval before review and CR extends the period of inactivity of patients, and medical attention for surgery-related complications is often sought during this period.^2–4^ Our prospective observational study (FORCAST6) found that 39% of patients reported surgery-related complications in the 6 weeks following discharge, with the majority occurring in the first 4 weeks; 15% required hospital readmission. Although the majority of patients were satisfied with the 6 weeks interval, 44% felt it was too long and would have liked an earlier review.^1^

The standard access for heart operations is through a median sternotomy.^5–8^ In the UK, 35 158 heart operations were performed in 2015.^9^ Following a median sternotomy, patients are required to refrain from upper body exercises, lifting of heavy objects and other strenuous activities for 12 weeks.^10–13^ These ‘sternal precautions’ (SP) are intended to aid healing of the sternum. CR, which has significant short-term and long-term benefits after cardiac surgery,^14 15^ is therefore delayed. The delay can mitigate the benefits of CR,^16^ contributing to physical deconditioning, and hinder the ability of CR to facilitate timely recovery of fitness and physical activity status.^17^ However, current guidelines for activity and exercise after median sternotomy have been described as restrictive, conflicting, sometimes arbitrary, frequently anecdotal and frequently at odds with modern clinical guidance.^11^

Following surgery, there are variations in types of exercises permitted, limits for weight of objects that can be lifted, guidelines for activities and timeline for resumption of driving. Parker *et al*^18^ demonstrated that the force elicited on the breastbone by coughing far exceeded lifting above the recommended limit. Adams *et al*^11^ investigated forces associated with 32 activities of daily living and reported that the majority not restricted by SP, such as opening and closing doors, generated forces greater than the allowed weight limit. While SP may help to support bone healing, the optimal nature and duration are unclear especially since sternal bone healing occurs by 5 weeks.^12^ According to the 2013 UK national audit of CR, late commencement contributes to a substantial number of heart surgery patients declining to participate.^19^ Adverse outcomes following heart operations and other forms of surgery have been shown to be reduced by early patient review after hospital discharge.^20 21^ The FORCAST6 study showed a high incidence of postoperative complications with the current 6-week patient review after heart surgery. This was the highest in the first week after hospital discharge and declined to lowest levels by 4 weeks.^1^ It, therefore, seems logical to conduct patient reviews after hospital discharge sooner than current practice to enable early CR from the period of postoperative stability and sternal bone healing at 5 weeks after surgery (4 weeks after hospital discharge).

The British Association for Cardiovascular Prevention and Rehabilitation (BACPR) Standards and Core Components^22^ and the National Certification Programme for CR^23^ recommend early commencement of CR. This is monitored by the National Audit of CR 2018.^19^ A delay in starting CR can prolong the recovery process, increase dependence on family/carers and can cause frustration. This may contribute to anxiety and depression that is reported in patients recovering after cardiac surgery.^24^

This study aims to examine the feasibility of bringing forward outpatient review and CR in order to facilitate recovery, physical fitness and quality of life.

## Methods and analysis

### Study design

A multicentre, randomised controlled, open feasibility trial using mixed methods to establish the feasibility of conducting a study where:

Participants have a postoperative outpatient review 6 weeks after hospital discharge, followed by commencement of CR from 8 weeks (control arm) orParticipants have a postoperative outpatient review 3 weeks after hospital discharge, followed by commencement of CR from 4 weeks (intervention arm).

The study is detailed in figure 1: study flow chart and the protocol follows the Standard Protocol Items: Recommendations for Interventional Trials reporting guidelines.^25^

**Figure 1 F1:**
[figure not shown]
FARSTER study flow chart. PIS, Patient Information Sheet.

### Study aim

To establish the feasibility of delivering and evaluating a definitive randomised controlled trial (RCT) of the current 8th vs 4th week CR commencement pathways, reducing the period over which patients are required to refrain from usual physical activities following cardiac surgery.

### Study objectives

The primary objective is to determine the feasibility of delivering outpatient review 3 weeks after discharge postcardiac surgery, followed by CR from 4 weeks.

#### Secondary objectives

Assess surgeons’ and surgical practitioners’ willingness to conduct outpatient review 3 weeks after discharge and refer patients to CR.Examine barriers to patient enrolment.Identify recruitment rates and drop-out to follow-up.Identify the most appropriate outcome measures.Test follow-up procedures and data collection tools and management.Assess the feasibility of conducting an economic evaluation of any future definitive RCT.Gather outcome data for power and sample size calculations for the RCT.Inform any necessary redesign of a new recovery pathway in light of information gained.

### Study population and setting

Patients attending for cardiac surgery at Hull University Teaching Hospitals National Health Service (NHS) Trust, UK and South Tees Hospitals NHS Foundation Trust, UK will be approached regarding study participation.

### Inclusion criteria

Undergone elective or urgent cardiac surgery, including the following procedures (isolated or combined):Coronary artery bypass graft (CABG).Aortic valve replacement.Mitral valve repair or replacement.Atrial fibrillation ablation.Left atrial appendage occlusion.Has had a full median sternotomy.Willing and capable of giving informed consent.Aged 18–80 years at the time of giving consent.Able to self-complete the English language outcome measure tools (or can complete with assistance).Able to follow detailed verbal instructions required for clinical assessments.

### Exclusion criteria

Body mass index (BMI) >45 kg/m^2^.Heart failure with left ventricular ejection fraction of <30% before surgery.Early postoperative sternal wound complications (eg, deep sternal wound infection, wound dehiscence and/or sternal instability).Postoperative complications resulting in prolonged hospital stay >14 days after surgery.

### Amendment to eligibility criteria

During the initial recruitment period, fewer patients than anticipated were meeting the eligibility criteria, and many were ‘out of area’ impacting on their ability to attend study CR locations. With the funder’s approval, a substantial amendment was submitted to the ethics committee. The original criteria had only included patients who had undergone CABG, had an upper age limit of 75 years and a maximum BMI limit of 40 kg/m^2^. This amendment was approved on 30 October 2019.

### Sample size

This study is a feasibility RCT and therefore does not have a primary outcome measure to inform a power calculation. Sample sizes of between 24 and 70 have been recommended for feasibility trials to allow for the reliable estimation of an SD for use in future sample size calculations.^26 27^ The plan is to recruit 100 eligible patients, allowing for a 30% attrition rate in order to still have 70 patients in the final analysis. There will be a 7-month recruitment period across two centres.

### Participant recruitment

Patients scheduled for elective cardiac surgery will be given the study leaflet prior to surgery. Patients undergoing urgent cardiac surgery will receive it following surgery. All patients will undergo surgery as normal, receiving standard in-hospital postoperative care.

### Eligibility and consent

After discharge from intensive care to the ward following surgery, the medical staff will review patients’ routine clinical examination results, including sternal stability and postoperative tests. Those identified as potentially eligible, interested and willing, will have their eligibility confirmed by the research nurse using an eligibility checklist and written informed consent will be obtained according to Good Clinical Practice guidelines. Consent will also be sought to contact participants who are interested in being interviewed as part of an embedded qualitative study.

Patients screened as eligible, but who develop complications between being considered ready for discharge and going home, will not proceed to consent until deemed well enough (if remain in hospital for >14 days after surgery, as per exclusion criteria they will not proceed at all).

### Randomisation

Following surgery, consent and completion of baseline data collection and assessments, participants will be randomised to either the control or intervention arm.

Randomisation will be performed by a remote, centralised randomisation service provided by York Trials Unit (YTU), and the allocation sequence generated by a statistician not involved in the study. Participants will be individually randomised and stratified according to study site on a 1:1 basis using variable block sizes. Authorised site research staff will telephone the randomisation service to obtain the participant’s allocation.

### Outcomes

Participant self-reported data will be collected at baseline, prior to CR commencement, following CR completion and at final follow-up assessment (up to 26 weeks postrandomisation):

Demographics (baseline only).EQ-5D-5L (EuroQol-5 dimensions-5 levels): a validated generic patient-reported outcome measure.^28^
NHS resource use.

The following clinical data will be collected:

Height, weight, BMI, preoperative presentation (baseline only).Heart rate, blood pressure, oxygen saturation at baseline, outpatient review and pre-CR as per usual practice.Physical fitness assessed by dynamic testing with incremental shuttle walk test (ISWT) for both study arms at commencement and end of CR, and at final follow-up.Cardiopulmonary fitness assessed by cardiopulmonary exercise testing (CPET) at baseline and at final follow-up, for up to 25 patients in each study arm (Hull study site only).30 and 90-day mortality, surgical site complications and hospital readmission rates.

In line with the objectives of a feasibility study, we will also gather information on:

Recruitment rates and drop-out to follow-up.Compliance to treatment arm allocation.Acceptability of patient recruitment, early outpatient review and CR to patients, clinicians and NHS organisations.

### Cardiopulmonary exercise testing

Maximal CPET provides a holistic assessment of the cardiovascular, ventilatory and metabolic responses to exercise and is a powerful diagnostic and prognostic tool.^29^ Maximal CPET is the gold-standard method of assessing changes in aerobic fitness, which is potentially important if we are to assess the beneficial/not harmful effects of early CR. Maximal CPET will be conducted on a cycle ergometer with patients pedalling at 50 revolutions per minute throughout the test. The test workload will start at 0watts and increase in 10watts/minute increments until the patient reaches volitional exhaustion (ideally 8–12 min^29^). Maximal CPET will only be carried out (after randomisation) in up to 25 participants in each arm in the Hull site only due to costs and logistics, but also to ensure that test procedures and data interpretation are consistent. CPET will be completed once a participant is deemed clinically stable and conducted within 14 days after surgery. It will be repeated at the final follow-up.

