### Blinding

By the nature of the timing of the study treatments, blinding of the participants and clinicians is not possible and a procedure for unblinding is not necessary. The clinician evaluating the CPET data will be blinded. The statistician and health economist will be blinded to study allocation.

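### The baseline CPET is scheduled after open randomisation, against the stated order of baseline assessments, so known allocation can affect who enters the Hull CPET subset and how hard they try

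*Protocol article*

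**What the plan says.** Three sections of the protocol article bear on when the first CPET takes place.

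- Randomisation: "Following surgery, consent and completion of baseline data collection and assessments, participants will be randomised to either the control or intervention arm". Site research staff then obtain the allocation by telephone.
- Outcomes: "Cardiopulmonary fitness assessed by cardiopulmonary exercise testing (CPET) at baseline and at final follow-up, for up to 25 patients in each study arm".
- Cardiopulmonary exercise testing: "Maximal CPET will only be carried out (after randomisation) in up to 25 participants in each arm in the Hull site only". The same section adds: "CPET will be completed once a participant is deemed clinically stable and conducted within 14 days after surgery".

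Table 1 does not settle the order. It puts the first CPET, baseline data collection and randomisation in one Week 0 column.

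Two other statements matter. The Blinding section says that "blinding of the participants and clinicians is not possible", although the clinician who evaluates the CPET data, the statistician and the health economist are blinded. The CPET section describes a workload that will "increase in 10watts/minute increments until the patient reaches volitional exhaustion".

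**The concern.** Read together, these sections give the same measurement two places in the sequence. If the CPET section is followed, the first CPET happens when the participant and the treating staff can already know the arm. Two routes for influence then open.

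- **Entry to the subset.** Someone must judge the participant clinically stable, and the subset is limited to 25 per arm. The article does not say that membership is settled before allocation.
- **Effort.** The test stops when the participant decides to stop. Someone who knows that rehabilitation will start in 4 weeks rather than 8 may push more or less hard.

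Blinding the evaluator protects the interpretation of the data. It does not protect entry or effort.

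The protocol gives CPET a particular role: "Maximal CPET is the gold-standard method of assessing changes in aerobic fitness". A change needs a sound starting value. The other fitness test, the incremental shuttle walk test, is first done before rehabilitation, at Week 4 in one arm and Week 8 in the other. CPET is thus the only fitness test scheduled at a common Week 0, and the only one that could supply a pre-randomisation value. Two secondary objectives, choosing outcome measures and gathering data for the definitive trial's sample size, draw on these results.

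**Working it through.** **1. The order of events, side by side**

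| Section | What it implies for the first CPET |
|---|---|
| Randomisation | Baseline assessments are complete, then allocation |
| Outcomes | CPET is a baseline assessment |
| Cardiopulmonary exercise testing | CPET follows allocation |
| Table 1 | Same Week 0 column as randomisation; order not shown |

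The first two rows put CPET before allocation and the third puts it after. The conflict is in the stated text and does not come from a detail left to another document.

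**2. Does the first test precede any difference in care?**

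Table 1 has surgery at Week −1 and discharge at Week 0. The limit of 14 days after surgery therefore falls at about −1 + 2 = Week 1. The arms first differ at the Week 3 outpatient review. The test is post-randomisation but pre-intervention, so only knowledge of allocation can act on it.

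**3. Does the cap of 25 per arm select?**

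The target is 100 participants over two sites, allocated 1:1 with stratification by site. The article gives no split between sites, so Hull's share is an assumption:

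| Hull recruits | Per arm at Hull | Left out by the cap, per arm |
|---|---|---|
| 50 | 50/2 = 25 | 0 |
| 60 | 60/2 = 30 | 5 |
| 70 | 70/2 = 35 | 10 |

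If Hull recruits about half, the cap hardly selects. It matters only if Hull recruits clearly more than half.

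**4. The plan's own figure, and the scale of the CPET subset**

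The recruitment target reproduces: 70/(1 − 0.30) = 100. No sample-size figure is in dispute.

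The standard error of a between-arm difference in means, in SD units, is √(2/n) with n per arm:

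- n = 25: √(2/25) = 0.28 SD. A difference within 1.96 × 0.283 = 0.55 SD is compatible with chance.
- If the trial's 30% attrition also applied to the subset (an assumption), 50 × 0.70 = 35 would have paired tests, or 17.5 per arm: √(2/17.5) = 0.34 SD.

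The trial's own data could therefore not reveal a moderate imbalance caused by known allocation.

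**5. Can the bias be sized?**

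No. The documents give no CPET SD, no expected refusal or deferral rate by arm, and no figure for an effect of effort.

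**The case against.** The strongest reply is that the CPET section makes a deliberate, specific exception to a general statement. The test comes before any difference in care, written consent precedes randomisation, and sternal stability and postoperative tests are reviewed before consent. The article describes no separate agreement to CPET after allocation, and the rule for choosing the subset may be in the full protocol. The trial has no primary outcome measure, analyses are descriptive, and feasibility is judged on consent, recruitment, retention and attendance, none of which depends on when CPET is done.

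Most of this stands, and it limits the consequences. It does not remove the conflict. If an exception is meant, the Randomisation and Outcomes sections should say so. Nor does it remove the route through effort, which needs only that the participant knows the arm.

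Two stronger readings are tempting.

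- **That the first CPET is unusable as a baseline, or that the CPET groups are no longer comparable.** The documents do not support this. No differential treatment has occurred by then, no covariate-adjusted CPET analysis is stated, and selective entry is possible but not shown.
- **That the bias is of a known, sizeable amount.** Suppose fitness is normally distributed and the least fit fraction p of one arm alone drops out on learning the allocation. That arm's mean then rises by φ(z_p)/(1 − p), with φ the standard normal density and z_p its p-quantile: 0.20 SD at 10%, 0.35 SD at 20% and 0.50 SD at 30%. The arithmetic is right, but the fractions are invented, and nothing in the documents suggests losses of that kind.

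**Conclusion.** The contradiction is certain: the Randomisation, Outcomes and CPET sections cannot all be followed as written. That known allocation could affect entry to the subset and effort in the test follows from open allocation, a discretionary stability judgement and a volitional end point. That it will do so is not shown, and its size cannot be derived.

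What is at risk is the comparability of the CPET subset between arms, and the CPET uptake, change and SD figures carried into the design of the definitive trial. The main feasibility measures and the randomised comparison of all 100 participants are unaffected, and no effectiveness test is invalidated because none is planned. A reader might infer that the CPET results would be worthless; that goes too far. This should be fixed because the remedy is cheap and a first test done after disclosure cannot be repeated later as a pre-randomisation baseline, but it does not threaten the trial as a whole.

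The verdict assumes that the participant learns the arm at or soon after the randomisation call. The article states open allocation and describes no step that withholds it until after CPET. That the person conducting the test knows the arm is an inference, and the verdict does not depend on it.

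**What to change.** Reconcile the Randomisation, Outcomes and CPET sections by replacing the words in the CPET section that place the test after randomisation. The new text should say:

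1. Hull participants are identified for the CPET subset before the randomisation call, by a stated rule; for example, consecutive consenting Hull participants up to 50 in total.
2. The first CPET is done before allocation is disclosed wherever the existing stability condition and 14-day window allow. Neither of these changes.
3. Where the test has to follow disclosure, it is labelled as post-randomisation but pre-intervention. It may still serve as the starting value, with its timing reported.
4. All subset members, tested or not, stay in the CPET summary by arm, so that uptake and missing tests are visible.

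Cost: a wording change and a different order of steps at one site. The sample size and the rehabilitation schedule stay as they are. The randomisation call may come slightly later for some Hull participants, which leaves less time to book the Week 3 review in the intervention arm. A cap on the total may not give exactly 25:25.
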